# 4.0 ELIGIBILITY ASSESSMENT

## 4. 1 Inclusion Criteria

- Age > 18 years old
- Ability to comprehend the investigational nature of the study
- Able to read and speak English
- Agrees to participate in the study
- Able to lift arms over head without pain
- Able to sit and stand from a seated position unassisted
- Intends to serve as an active caregiver* for a patient undergoing their 1^st^ allogeneic HSCT at the NIH Clinical Center

## Exclusion criteria

- - - Age < 18 years old
    - Pregnant or lactating women
    - Inability to comprehend investigational nature of study
    - Inability to provide informed consent
    - Unable to read and speak English
    - Does not agree to participate in study or follow study design
    - Serving as a paid caregiver for any individual
    - Regular practitioner of yoga, meditation or other mind-body practice (definition: taking classes or practicing at least weekly for at least 2 of the past 6 months).
    - Physical function limitations that would interfere with intervention

Caregiver participants will be excluded from the biomarker analysis if they have had:

- - - Glucocorticosteroid treatment in the last 2 months
    - Have a recent (within the last 2 months) acute illness or injury
    - Have served as a stem cell transplant donor or have taken filgastrim

*****If more than one caregiver is planned for the transplant recipient during the transplant phase, only 1 caregiver will be eligible to participate in the study. An active caregiver is defined as someone who lives with or provides care regularly for the HSCT recipient during the 6 week study period. Caregivers will be categorized as to whether they are the sole caregiver versus one of multiple caregivers.

# 5.0 METHODS

## 5.1 Questionnaires:

5.1.1 Caregiver Reaction Assessment

5.1.2 NIH Toolbox/Neuro QOL Measures

5.1.3 Health-Promoting Lifestyle Profile II

5.1.4 PROMIS^®^ Measures

5.1.5 Pittsburgh Sleep Quality Index

5.1.6 Freiburg Mindfulness Inventory-Short form

5.1.7 Multidimensional Fatigue Symptom Inventory- Short Form (MFSI-SF)

**5.1.1 Caregiver Reaction Assessment (CRA)**

The CRA is designed to assess the positive and negative effects of caregiving for persons providing care to patients with chronic illnesses. The measure consists of 24 items that comprise five subscales including: caregiver esteem, lack of family support, impact on finances, impact on schedule, and impact on health. Participants indicate their agreement with the given statements on a 5-point Likert Scale ranging from “strongly disagree” (1) to “strongly agree” (5) with higher scores denoting a greater impact of the attribute for the caregiver.

In addition to a sample of caregivers of Alzheimer’s patients, the initial testing of the scale included an evaluation of its effectiveness among a sample of 276 caregivers of cancer patients undergoing active treatment for a new or recurring solid tumor or lymphoma [^56^](#_ENREF_56). Internal consistency for the subscales ranged in correlation from 0.80 to 0.91, indicating high reliability. Construct validity has been supported through strong correlations with the Center for Epidemiologic Studies Depression Scale (CES-D Depression Scale) [^57^](#_ENREF_57) and the Activities of Daily Living Dependency Scale (ADL Dependency Scale) [^58^](#_ENREF_58).

**5.1.2 NIH Toolbox and Neuro QOL Measures**

NIH Toolbox and Neuro QOL are a multidimensional set of brief measures assessing cognitive and emotional function from adults. Stress and Self-Efficacy focus on individual perceptions about the nature of events and their relationship to the perceived coping resources of an individual. In general, psychological stress is said to occur when an individual perceives that environmental or internal demands that are personally meaningful exceed his or her adaptive capacity. Operationally, psychological stress is defined by individual reports of adaptive capacity overload. However, it has been defined by the presence of a stressor deemed taxing by consensus, for example, the death of a close other. If the electronic system is unavailable, and the three questionnaires normally given as computer-adaptive tests**are given as hard copy questionnaires, they will be scored in accordance to the comparable short form (fixed item questionnaire). Reliability for this scale has been consistently high with Cronbach’s alphas ranging from 0.91 to 0.95 [^59^](#_ENREF_59).

- Loneliness Short Form
- Self-Efficacy**
- Perceived Stress **
- Positive Affect & Well-being**

**5.1.3 Health-Promoting Lifestyle Profile II (HPLP-II)**

Walker and Hill-Plorecky [^60^](#_ENREF_60)^,^[^61^](#_ENREF_61) developed the HPLP-II, which is a self-administered 52-item instrument that measures the frequency of self-reported healthy behaviors. It consists of 6 subscales: physical activity, spiritual growth, health responsibility, interpersonal relations, nutrition, and stress management. This is a 4-point Likert type scale with responses ranging from 1 (never) to 4 (routinely), and the possible scores ranging from 52 to 208. The higher scores indicate the more frequent engagement in health behaviors. Callaghan [^62^](#_ENREF_62) reported the following Cronbach’s alpha coefficients of internal consistency reliability: total scale 0.93, health responsibility 0.83, physical activity 0.87, nutrition 0.76, spiritual growth 0.84, interpersonal relations 0.82, and stress management 0.75.

**5.1.4 PROMIS^®^ Measures**

Patient-Reported Outcomes Measurement Information System (PROMIS^®^), is an initiative based on an NIH grant to establish and provide the public a free, valid and reliable (Cronbach’s alpha ranging from 0.76-.96) measures for a variety constructs [^63^](#_ENREF_63)^,^[^64^](#_ENREF_64). The PROMIS^®^ item databanks have been tested for reliability and comparability to more established measures of these same content areas by NIH scientists and select US academic institutions using Item-Response Theory [^65^](#_ENREF_65). If the electronic system is unavailable, and the three questionnaires normally given as computer-adaptive tests** are given as hard copy questionnaires, they will be scored in accordance to the comparable short form (fixed item questionnaire).

- Anxiety**
- Applied Cognition – General Concerns**
- Depression**

**5.1.5 Pittsburgh Sleep Quality Index (PSQI)**

The PSQI is an 18 item self report measure of subjective sleep quality [^66^](#_ENREF_66). Clinical information about sleep parasomnias (such as snoring, restless legs, and sleep apnea) is assessed by the bed partner in 5 additional questions that are not used in the scoring. Items for the PSQI were generated from a review of existing questionnaires and from clinical experience, and the instrument underwent 18 months of initial field testing [^66^](#_ENREF_66). Response format is on a four point scale, with 0 = no difficulty and 3 = severe difficulty. The response frame is over the past month; although a modification of the instrument assessing subjective sleep quality over the past week has also been utilized[^67^](#_ENREF_67). The PSQI takes approximately 5-10 minutes to complete. Responses to the 18 items are grouped into seven equally weighted component scores. The component scores measure the domains of subjective sleep quality, sleep latency, sleep duration, habitual sleep efficiency, sleep disturbances, use of sleeping medications, and daytime dysfunction. The 7 component scores can be summed to produce a global score ranging from 0-21. Higher scores indicate more severe complaints and worse sleep quality [^66^](#_ENREF_66). There is strong support for the psychometric properties of the PSQI in a variety of clinical populations and in research [^67-78^](#_ENREF_67). Internal consistency reliability in samples of patients with cancer ranged from 0.70 to 0.81 [^67^](#_ENREF_67)^,^[^70^](#_ENREF_70). Relative to construct validity, a global PSQI score >5 provided a sensitive and specific measure of poor sleep quality compared with clinical and polysomnographic measures [^66^](#_ENREF_66).

**5.1.6 Freiburg Mindfulness Inventory-Short Form**

The Freiburg Mindfulness Inventory-short form is a 14-item self- administered questionnaire that is designed to measure the concept of mindfulness, defined as an awareness and friendly acceptance of one’s mental processes including sensations, perceptions, cognitions, and affects [^79^](#_ENREF_79). Designed to be used in the general population with individuals not necessarily familiar with mindfulness or Buddhist concepts, the short form was derived from the 30-item Freiburg Mindfulness Scale, and it has good reliability and validity compared to the original scale (Cronbach’s alpha = .86) [^79^](#_ENREF_79). Higher scores indicate higher levels of mindfulness.

**5.1.7 Multidimensional Fatigue Symptom Inventory- Short Form (MFSI-SF)**

The MFSI-SF is a 5 point Likert-scale used to assess various dimensions of fatigue. Though originally created for use with cancer patients, the measure have been effectively used with other populations due to its non-disease specific characteristic[^80^](#_ENREF_80). Among the populations that have utilized this scale include patients with various cancers, orofacial pain populations, and healthy subjects[^81-83^](#_ENREF_81).

The MFSI-SF contains 30 items derived from the original 82-item MFSI. Subjects are asked to rate their level of fatigue in the past week on a scale ranging from 0 (not at all) to 4 (extremely). A total of five fatigue subscales make up the measure including: general, physical, vigor, emotional, and mental. Reliability and validity have been established in multiple studies. The original study indicated significant internal reliability for each of the subscales with alpha coefficients ranging from 0.87 to 0.96[^80^](#_ENREF_80). In accordance, validity is significantly high. To demonstrate concurrent validity, the MSFI-SF was measured against the Fatigue Symptom Inventory (FSI) and the SF-36 Vitality Scale and convergent validity was established using the SF-36 Physical Composite score.

## 5.2 Demographic Interview Appendix C

A demographic interview will assess basic demographic information about the caregiver subject including employment status, living arrangements, caregiving hours, concurrent caregiving obligations, whether the caregiver is a sole caregiver or one of multiple caregivers, quantitative alcohol and tobacco consumption, and occupation.

## 5.3 RESEARCH PARTICIPANT/PATIENT DATA

**5.3.1. Transplant recipient data:**

A waiver of consent (see section 10.3.1) is requested to obtain non-research clinical data on the HSCT patient (care recipient) who is receiving HSCT treatment at the NIH and is the associated patient for whom the enrolled caregiver is providing care. This information will be collected from the Clinical Research Information System (CRIS record only) on the patient and includes: disease, stage of disease, date of treatment, type of treatment, treatment protocol, inpatient hospital length of stay, total hospital days during study period, number of readmissions, frequency of outpatient visits for clinical care and total days as outpatient during the caregiver subject’s participation in this study. These data will be used to characterize the caregiver’s experience.

**5.3.2 Caregiver participant data**

A complete medical history, physical exam, review of current medications, assessment of recent stressful life events, and ECOG performance status. Medications will be classified into several categories to include: diabetic, cardiovascular, central nervous system active medications, non-steroidal anti-inflammatory, and other. Additionally data collected will be used to determine their co-morbidity index score and will be calculated using the Charleson Co-morbidity index score [^84^](#_ENREF_84). The Charleson Co-morbidity index score determines an individual’s 10 year risk for mortality by assigning a numerical score to one’s co-morbid conditions to determine a combine score for overall risk for mortality.

## 5.4 Clinical and Laboratory Assessments

**5.4.1 Clinical Assessments**

A complete medical history, physical exam and review of current medications, smoking and alcohol consumption, measurement of height, weight, blood pressure, heart rate, and waist circumference. Participants will be weighed in light clothing without shoes to the nearest 0.1 kg and their heights, in centimeters (cm). Body mass index (BMI) will be calculated using the following calculation:

$$\text{BMI=weight}\frac{\text{kg}}{\left[ \text{height }\left( \text{cm} \right) \right]\text{2}}$$

Waist circumference will be measured at the level of the umbilicus with the participant in mid-expiratory position. Blood pressure, measured by Dinamap^®^ Pro 100-400v2 electronic blood pressure machine or by manual sphygmomanometer on either the right or left upper arm of the participant following a 5-minute rest period in a sitting position. Clinic staff obtaining measurements on study participants will be educated on the techniques to obtain measurements for this study.

The presence of metabolic syndrome will be determined based on the NCEP ATP III [^48^](#_ENREF_48). Subjects will be categorized as ‘positive’ if three or more of the following are present: hyperglycemia (fasting blood glucose ≥ 110 mg/dL), hypertension (BP≥130/85 mmHg), hypertriglyceridemia (triglycerides>150 mg/dL), low High-Density Lipoprotein Cholesterol (HDL<40 mg/dL in men and <50 mg/dL in women), and waist circumference >40 inches in men and >35 inches in women. If three or more are not present, subjects will be categorized as ‘negative’ relative to metabolic syndrome.

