## Exploratory Objectives

- - - 1. To examine whether HSCT caregivers participating in a stress reduction intervention demonstrate improvement in certain individual factors (self-efficacy, burden, and mindfulness), psychosocial factors (stress, anxiety, depression, loneliness, positive affect and well-being), behaviors (health behaviors) and symptoms (sleep, fatigue, depression, and cognitive impairment) compared with HSCT caregivers in the control group.
      2. To examine whether HSCT caregivers participating in a stress reduction intervention demonstrate improvement in physiological markers of stress (serum cortisol) and clinical (blood pressure, waist circumference, body weight) and biomarkers of inflammation and cardiometabolic disease (lipids profiles, fasting blood glucose, insulin, IL6, TNF-alpha, hs-CRP) compared with HSCT caregivers in the control group.
      3. To examine whether the amount of yoga practiced by HSCT caregivers in the intervention group contributes to improvement in individual factors, psychosocial factors, behaviors, symptoms, as well as physiological markers of stress and clinical and biomarkers of inflammation and cardiometabolic disease.
      4. To characterize subjects with a significant change in perceived stress or other study outcomes (ie: sleep disturbance, depression, anxiety, loneliness) following the intervention, to generate possible hypotheses for future research.

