All participants will receive usual care education (UCE), which includes transplant specific information for the recipient and the caregiver, as well as caregiver resources. After study enrollment, caregiver subjects will be randomized to either the control group or the intervention group. A permuted block randomization with allocation ratio of 1:1 will be performed by the study statistician. All participants will meet 1:1 with a study investigator to review the UCE materials. Participants in the intervention group will also receive an audio recording of a 20 minute yoga-based stress reduction intervention, as well as instructions on how to complete the intervention; they will be asked to practice the twenty minute audio file daily for the six weeks of the intervention. The six-week length of the intervention, as well as the 20 minute time of the audio file, was selected based upon the length of similar interventions in other caregiver populations, with interventions ranging between four to ten weeks [^37^](#_ENREF_37)^,^[^43^](#_ENREF_43). All study visits will be scheduled around the HSCT recipient’s schedule and visits to minimize burden for the caregiver. The initial visit for all participants will occur prior to the patient’s initial discharge from the hospital and within 7 days of the HSCT infusion (Day 0+7). Subjects in the intervention group will receive a brief phone call at weeks two and four (+/- 7 days) to assess progress and to record practice. All subjects will participate in an exit interview at week six (+/- 7 days). Study questionnaires will be administered to all subjects at baseline and again at week six (+/- 7 days). Completion will take approximately 20 minutes through a web-based system. If the electronic system is unavailable, a hard copy of the questionnaires will be available for completion. Caregivers in either group who complete baseline assessments but are no longer able to return to the clinical center for their week 6 study visit will be given the option to complete the week 6 questionnaires electronically.

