***Instructions for blood sampling:***

Study participants will be instructed verbally and given the following written instructions to prepare for blood sampling. Please report to the outpatient phlebotomy area for blood work in the morning. Please do not eat for 10 – 12 hours before blood work collection.

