**5.4.3 Laboratory Sample Routing**

The following samples will be sent for processing in the **Clinical Center Department of Laboratory Medicine:**

Lipid panel, NMR analysis**,** Apolipoprotein panel (Apo A-1, Apo B, Apo B/Apo A-1), serum cortisol, hs-CRP.

The following laboratory samples will be sent for processing to **[name] research lab, [name]:**

TNF-α, IL-6.

##

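### Blood pressure device and arm, and the clock time of the blood draw, need not match between baseline and week 6, which costs precision in two exploratory comparisons

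*Protocol*

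**What the plan says.** - **Blood pressure (Section 5.4.1).** It may be taken by an "electronic blood pressure machine or by manual sphygmomanometer on either the right or left upper arm of the participant". Rest and posture are fixed: the reading comes "following a 5-minute rest period in a sitting position". On the staff, the section adds: "Clinic staff obtaining measurements on study participants will be educated on the techniques to obtain measurements for this study".
- **Blood draw (Section 5.4.2, sampling instructions).** On timing, caregivers are told: "Please report to the outpatient phlebotomy area for blood work in the morning". On fasting, the instruction is: "Please do not eat for 10 – 12 hours before blood work collection". No clock window is given. Section 5.4.3 sends the cortisol sample to the clinical laboratory with the other routine assays.
- **Use of the measures (Exploratory Objectives, objective 2).** The trial looks for "improvement in physiological markers of stress (serum cortisol) and clinical (blood pressure, waist circumference, body weight" and other markers, relative to control.
- **Visit timing (Section 3.0).** Study visits are fitted round the recipient's own timetable and "visits to minimize burden for the caregiver". Week 6 carries a window of 7 days either side.
- **Occasions of measurement.** The Precis plans a physical assessment at baseline and again at the end of the six weeks. In Figure 3 the Clinical Assessment row is marked in the two baseline columns and is empty at week 6.
- **Analysis (Section 6.2).** Exploratory outcomes go into linear mixed models. The covariates named for adjustment are demographic.

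**The concern.** Objective 2 depends on change within a caregiver between two visits. A different device, arm or draw time at the second visit enters that change as error unrelated to stress. The protocol treats measurement conditions as its own business, since it fixes rest, posture, fasting and staff training. On device and arm it expressly permits either option at any visit. On draw time it stops at the morning.

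Baseline falls before the recipient's initial discharge and week 6 is about six weeks later, so equipment, staff and timing could plausibly differ between the two visits. Cortisol is the only analyte listed under stress markers in Section 5.4.2. Blood pressure also feeds the 130/85 limb of the metabolic syndrome classification. What is at stake is the ability of these exploratory comparisons to show a real difference. The conditions of a reading cannot be reconstructed later if they were not recorded.

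**Working it through.** **1. The plan's own figure.** Section 6.1 gives 39 per group for perceived stress (effect size 0.6, correlation 0.80, two-sided 0.05, power 80%). Taking the mean of two exchangeable time points:

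n = 2 × [(1 + 0.80)/2] × (1.960 + 0.842)² / 0.6² = 2 × 0.9 × 7.849 / 0.36 = 39.24 per group.

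This reproduces 39 to the nearest whole number (power at 39 is 79.8%). Perceived stress is a questionnaire score, so device, arm and draw time do not enter it. Section 6.1 says that power was worked out for the primary objective only.

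**2. What is fixed and what is not.**

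| Condition | Stated | Tied to baseline at week 6 |
|---|---|---|
| Posture and rest (blood pressure) | seated, 5 minutes | same rule for every reading |
| Device | either of two | no |
| Arm | either | no |
| Fasting (blood) | 10–12 hours | same rule for every draw |
| Clock time (blood, including cortisol) | morning | no |

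**3. How the error enters.** Let a reading have variance σ² under matched conditions, with correlation r between visits. Let unmatched conditions add independent variance kσ² at each visit. Then

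Var(change) = 2(1 − r)σ² + 2kσ², so the variance inflation is 1 + k/(1 − r).

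**4. Plausible k.** The protocol gives no SD for blood pressure, no device or arm difference, and no rate of change for cortisol. All inputs in this step are assumptions.

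- Blood pressure: SD 15 mmHg; device difference D of 3 to 8 mmHg; arm difference A of 0 to 5 mmHg; each chosen at random (probability one half) at each visit. Added variance is D²/4 + A²/4.
  - Low: 9/4 + 0 = 2.25; 2.25/225 = 1%.
  - High: 64/4 + 25/4 = 22.25; 22.25/225 = 9.9%.
- Cortisol: decline g of 0.1 to 0.3 SD per hour; draw times uniform over W = 1 to 4 hours. Added share is g²W²/12.
  - Low: 0.01 × 1/12 = 0.1%.
  - High: 0.09 × 16/12 = 12%.

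If in practice one device and one arm are always used, and draws are always at the same hour, k is zero.

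**5. Effect on precision.** The detectable difference in change at 39 per group is (1.960 + 0.842) × √(2 × Var(change)/39), in units of σ. The correlation of 0.80 in Section 6.1 belongs to perceived stress, so r is varied.

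| r | k | Variance inflation | Detectable difference |
|---|---|---|---|
| 0.5 | 0 | 1.00 | 0.63 |
| 0.5 | 0.05 | 1.10 | 0.67 |
| 0.5 | 0.10 | 1.20 | 0.70 |
| 0.8 | 0 | 1.00 | 0.40 |
| 0.8 | 0.05 | 1.25 | 0.45 |
| 0.8 | 0.10 | 1.50 | 0.49 |

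At k = 0.01 the inflation is only 1.02 (r = 0.5) or 1.05 (r = 0.8). Adjusting for baseline instead of analysing change gives slightly smaller inflation, for example 1.44 in place of 1.50 at r = 0.8, k = 0.10.

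**6. When it would become bias.** If the device difference is D and the groups differ by p in the proportion measured manually at week 6, the group difference shifts by D × p. With equal use (p = 0) the shift is zero. With D of 3 to 8 mmHg and p of 10 to 30 points it is 3 × 0.1 = 0.3 to 8 × 0.3 = 2.4 mmHg. The protocol gives no reason to expect p to differ from zero.

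**The case against.** The strongest reply is that this is operating detail for exploratory outcomes. Rest, posture, staff training, a morning draw and a bounded fast are all specified. Appendix B refers to a manual of procedures, not shown here, which may well settle device, arm and time. Randomization at 1:1 means that conditions unrelated to group cost precision without biasing the comparison. Every magnitude rests on unsourced inputs, and the low end is negligible.

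Most of this stands, and it sets the weight of the point. It does not remove it. The protocol text permits either device and either arm, so a manual could only narrow a rule that is written too loosely. Nor do the covariates named in Section 6.2 include draw time, device or arm.

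A reader might go further and infer that unblinded staff bias the change outcomes. The documents do not support that:

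- The protocol does not say whether the clinic staff who measure blood pressure know the allocation. Appendix B lists them separately from the study staff who deliver the intervention.
- Section 3.2 places baseline measures before randomization, so only a manual week-6 reading could be affected.
- Section 5.4.3 lists "Apo B/Apo A-1), serum cortisol, hs-CRP" among the assays run by the Clinical Center laboratory, so no observer reads a cortisol value at the visit.

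A reader might also take cortisol and blood pressure as the trial's only physiological evidence. Objective 2 classes blood pressure as clinical and also lists inflammatory and metabolic markers.

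**Conclusion.** The point holds as a minor one. The stated rules leave device, arm and draw time free to differ between visits, which adds avoidable error and lowers precision for the exploratory blood pressure and serum cortisol comparisons. No definite loss of effective sample size can be claimed, because the protocol supplies none of the inputs. On the assumptions shown, the effect runs from negligible to a change variance up to about one half larger for blood pressure (k about 0.10, r = 0.8), and up to 1 + 0.12/0.2 = 1.6 times as large for cortisol. Observer bias is possible for manual week-6 blood pressure readings and is not shown. The primary outcome and the total of 78 are not touched.

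One related conflict comes first in practice. Figure 3 schedules no clinical assessment at week 6, while the Precis plans one and objective 2 needs a second blood pressure. Until these are reconciled, there may be no second reading to match.

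**What to change.** - **Section 5.4.1:** record device and arm at baseline and use the same ones at week 6. Make the automated device the default and flag any manual reading on the case report form. State whether the staff who measure blood pressure are masked to group.
- **Section 5.4.2:** record the clock time of every draw and schedule the week-6 draw near the baseline time where feasible.
- **Section 6.2:** include draw time as a covariate in the cortisol model for all subjects. Adding it only for those who miss a time window would make the model depend on compliance seen after randomization. Tabulate draw time, device and arm by group, so that any imbalance is visible.
- **Figure 3, the Precis and objective 2:** reconcile them so that a week-6 blood pressure is scheduled.

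The cost is a few sentences, a few case report form fields and slightly less freedom in timing the week-6 draw. That freedom matters because visits follow the recipient's schedule, which is why draw time is matched only where feasible.
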